## Abstract

Background

Neonates, particularly if born preterm or with congenital anomalies, are among the pediatric patients most likely to need blood transfusion. However, they are also particularly vulnerable to adverse consequences of blood transfusion. Aiming to clamp the umbilical cord for at least a minute after birth is a simple safe procedure that is being increasingly adopted worldwide, although may be associated with increased rates of polycythemia and jaundice. It may also reduce the proportion of preterm babies who need a blood transfusion. The mechanisms for this are not fully understood. Potential mechanisms could include an increased volume of blood transfusion from the placenta to the baby after birth, and an overall reduction in the severity of illness in the first weeks after birth, which could lead to fewer blood tests and greater tolerance of anemia, or enhanced erythropoiesis.

Objectives

To investigate the mechanism behind the reduced need for blood transfusions after deferral of cord clamping.

Methodology

This protocol outlines the methods and data analysis plan for a study using nested retrospective data from a large randomized trial combined with additional data collected from patient medical and pathology records. The additional data items to be collected all relate to the receipt of transfusion and the factors that affect the risk for transfusion in preterm babies. The analysis will include all randomized babies from Australia and New Zealand for whom data are available. Causal mediation analysis is planned to estimate the effects of mediators on the relationship between the timing of cord clamping and the need for blood transfusion. The analysis is designed to discern whether initial severity of illness or the magnitude of placental transfusion mediates red blood cell transfusion dependence.

Anticipated outcomes and dissemination

We expect the study will identify potential strategies for reducing blood transfusions and associated negative outcomes in preterm infants. This will be relevant to researchers, clinicians, and parents. The results will be disseminated through publications, presentations, and inclusion in evidence-based guidelines.

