Observational studies suggest that exposure to blood transfusion itself is harmful to preterm babies, increasing the risk of adverse outcomes [10]. However, this suggestion has not been supported by the small number (to date) of randomized controlled trials of blood (red cell) transfusion thresholds [11-14]. It is unlikely to be the means by which DCC reduced deaths in the largest trial to date of deferred cord clamping in preterm babies, the Australian Placental Transfusion Study (APTS), and in the most recent systematic review on this, because neither showed a difference in rates of other adverse outcomes [6,15].

Another possibility is that it is the umbilical cord blood stem cells received by the baby are the main reason for the observed benefits to both survival and reduced requirement for later blood transfusion [16]. Umbilical cord blood has been demonstrated to be such a good contributor to hematopoiesis that it is a recognized stem cell resource for pediatric and adult hematopoietic stem cell transplant [17]. In addition, umbilical cord blood is a potential regenerative and immunomodulatory agent for a variety of clinical conditions [18], so in this case, the extent of placental transfusion would be critical to the improvement of outcomes, and transfusion with adult red cells would not suffice. There are no established methods to quantify the contribution of umbilical cord stem cells to placental transfusion. However, a larger volume of placental transfusion results in the baby receiving more nucleated cells [19], including more umbilical cord stem cells.

Discerning whether these effects (initial enhanced cardiovascular stability leading to early and sustained reduction in severity of illness or volume of placental transfusion) appear to be the main driver of improved outcomes is likely to contribute to practice change, as well as to informing the design of future research studies into methods to improve outcomes of high-risk newborn babies and reduce their transfusion dependence.

The causal mechanisms of reduced transfusion requirements found in DCC relative to ICC are yet to be resolved. The aim of the study is to address the question; In preterm infants (P) does DCC (I) compared to ICC (C) reduce dependence on red cell transfusion via enhanced cardiovascular stability (mediator 1, M1) or via an increased volume of placental transfusion (M2).

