The intervention consisted of either immediate or delayed cord clamping (as assigned in APTS). Immediate clamping was defined as clamping the cord within 10 seconds of delivery. Delayed clamping was defined as clamping the cord at least 60 seconds after delivery, with the infant held as low as possible, below the introitus or placenta, and with no palpation of the cord. Variations in the protocol were allowed if they would aid the mother, baby, or both. If the baby was non-vigorous (heart rate <100 beats per minute, low muscle tone, or lack of breathing, or crying), clinicians were allowed to break protocol using their discretion. Cord milking was not part of the protocol for either intervention. Further details may be sourced from the original APTS publication [15].

Outcomes

The primary outcome is the proportion of babies receiving red cell transfusion (for restoration of hemoglobin or blood volume). The secondary outcomes are number of transfusions per baby, cumulative transfusion volume (mL/kg) per baby, and primary reasons for each transfusion.

Putative Mediators

M1: Indicators of placental transfusion to be assessed will be hematocrit (on admission, highest on the first day, highest in the first week collected before any postnatal transfusion).

M2: Indicators of initial severity of illness to be assessed will be cumulative blood sample volume collected throughout hospital stay (number of blood tests multiplied by hospital’s usual sample volume for each type of test), sampling line (umbilical arterial line or peripheral arterial line) - yes/no and total duration, mechanical ventilation or inspired O2, and blood pressure.

Sensitivity Analyses (For the Primary Outcome Analysis Only)

Sensitivity analyses will adjust for the following variables: gender, birth <27 weeks vs. ≥27 weeks, method of delivery (vaginal versus cesarean), intraventricular hemorrhage (IVH) (yes/no and grade III/IV yes/no), surgery for patent ductus arteriosus (PDA), necrotizing enterocolitis (NEC), and sodium in the first 24 hours of life. We will also test model assumptions relating to sequential ignorability and post-randomization confounding (discussed further in the data analysis plan).

Potential Confounders (Covariates)

The following covariates may be used for adjustment in the analysis: gestational age at randomization before birth and any oral iron supplement pre-transfusion.

Timing of Assessments

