Putative mediating variables will only be analyzed if they have been measured before the outcome and will be excluded if there is not adequate time and date information available. If the multiple mediator model is applied, careful consideration of timing information will be evaluated. If there is insufficient empirical information to conclude the causal ordering of mediators (M1 causes M2), we will adjust our analytic approach (as discussed in the analysis plan) and discuss any limitations.

Data Analysis Plan

The analysis will include all babies who were initially randomized in the APTS trial for whom we were able to obtain the relevant data and be based on intention-to-treat. All statistical analyses will be conducted in R version 4.1.3 (2022-03-10; R Foundation for Statistical Computing, Vienna, Austria). Descriptive characteristics for continuous data will be presented as means or medians, as appropriate, and categorical data will be presented as frequencies and percentages.

A model-based inference approach will be applied to estimate the average causal mediation effect (ACME), average direct effect (ADE), and the average total effect as recommended [23-25]. This approach will be applied with the R “mediation” package [26]. We will initially fit two models, one model with mediation as the dependent variable and intervention as the independent variable (mediator model), and a second model with the outcome as the dependent variable, and both mediation and intervention as independent variables (outcome model). To account for the clustering of multiples, estimates will be calculated with generalized estimating equations with a compound symmetric correlation structure to account for within subject correlations. Depending on the outcome (binary, count, skew) these will be modelled with the appropriate family and link functions.

A counterfactual framework will be applied to the mediator and outcome models to simulate the values of the mediator and outcome to estimate the potential values of the mediator. This process is used to estimate the ACME, ADE, and average total effects; 95%CI will be estimated with 1000 bootstrap simulations.

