## Discussion

Blood transfusions of neonates have been associated with a number of serious adverse outcomes [29]. Nevertheless, there are few evidence-based methods to reduce transfusion exposure [30]. The APTS study found that DCC was associated with a statistically significant reduced need for red cell transfusions by about 10% compared to ICC [15]. However, the mechanism remains unclear. 

The study will, at a minimum, provide further information that should increase clinicians’ understanding of the pathways by which DCC (or other methods to accomplish placental transfusion) results in beneficial patient outcomes. Since one of the main barriers to implementation is lack of understanding about the mechanisms by which such a simple practice change should have such dramatic effects, this should improve adherence to recommendations to defer cord clamping for most babies, thereby reducing mortality and transfusion incidence.

By elaborating on the mechanisms, it may also provide good evidence for how other routine neonatal intensive care practices and interventions affect likelihood of needing to transfuse. Better understanding of these effects may lead to other testable hypotheses or improvements in other aspects of practice, further reducing transfusion exposure and improving other outcomes.

Potential limitations of the study include the dependence on some routinely collected clinical data, which were not collected at the time by the original study according to predefined research definitions. However, we have no reason to think that potential problems of data quality would have been influenced by study group allocation and so do not anticipate that this will be a source of bias.

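### Death before any transfusion is not handled as a competing event, although the protocol says deferred clamping reduced deaths and the question is about need for transfusion

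*Protocol article*

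**What the plan says.** Under Outcomes, the protocol article states: "The primary outcome is the proportion of babies receiving red cell transfusion", whether given to restore hemoglobin or blood volume. It continues: "The secondary outcomes are number of transfusions per baby, cumulative transfusion volume (mL/kg) per baby", plus the reasons for transfusion. Table 1 uses any transfusion, volume and number as the outcome in every mediation model. The Data Analysis Plan sets the population: "The analysis will include all babies who were initially randomized in the APTS trial for whom we were able to obtain the relevant data", by intention to treat. Nothing restricts this to survivors or sets an exposure time.

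The target is set out in the Abstract, where mediation analysis is to "estimate the effects of mediators on the relationship between the timing of cord clamping and the need for blood transfusion". The Objectives likewise speak of transfusion requirements.

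On death, the Introduction discusses "the means by which DCC reduced deaths in the largest trial to date of deferred cord clamping in preterm babies", meaning the trial in which this cohort was randomized. The Discussion expects wider use of deferred clamping, "thereby reducing mortality and transfusion incidence". Death does not appear among the sensitivity analyses, in the missing-data text, or under post-randomization confounding, where non-adherence is the only example given.

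**The concern.** A baby who dies before any transfusion has received none, so the plain reading of the definitions gives no on the primary outcome and zero on number and volume. That is a correct record of transfusions received. It is not evidence that the baby had no need of one, and need is what the study sets out to explain.

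Two features make this more than a formality here. On the authors' own account, treatment affects the competing event. And one of the two rival mechanisms is severity of illness, which plausibly also drives early death. The babies in question may therefore sit at one end of the severity mediator with an outcome of zero, where they have leverage on the mediator-outcome slope and so on the indirect effect. At stake is how far the total effect, and the split between severity and placental transfusion, can be read as statements about need.

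**Working it through.** The protocol states no death rate, event count or power, so there is no figure of its own to reproduce. What follows is a range under stated assumptions.

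**Total effect.** Let p be the risk of transfusion had no baby died untransfused, d the share dying untransfused, and c the would-be risk among those babies. Coding them as not transfused gives

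observed risk = p - d × c.

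From the document: a risk difference (RD) of -0.07 in the systematic review cited in the Introduction. Assumed: p = 0.60 (ICC) and 0.53 (DCC), all values of d, and c between p and 1. Example: d = 3% and 2% with c = 1 gives 0.57 and 0.51, so RD = -0.060.

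| Untransfused deaths, ICC / DCC | RD, c = p | RD, c = 1 |
|---|---|---|
| 0 / 0 | -0.070 | -0.070 |
| 1.0% / 0.7% | -0.068 | -0.067 |
| 3% / 2% | -0.063 | -0.060 |
| 5% / 3.5% | -0.059 | -0.055 |
| 4% / 2% | -0.057 | -0.050 |

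The loss runs from about 3% (0.0677 against 0.070) to 29% (0.050 against 0.070). In babies, with 1401 enrolled and about 700 per arm assumed, 1%, 3% and 5% are about 7, 21 and 35.

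The Discussion gives the parent-trial reduction as about 10% without saying whether this is relative or absolute. Over the same death rates, 0.60 against 0.54 gives RDs from -0.058 to -0.040 (true -0.060), and 0.60 against 0.50 gives -0.098 to -0.080 (true -0.100).

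**Direction.** The pull toward the null needs more untransfused deaths with ICC, which does not follow from fewer deaths overall with DCC. If 10% die with ICC and 30% of those are untransfused, d = 3.0%. If 7% die with DCC and 43% of those are untransfused, d is again 3.0%. With c = 1 the RD then stays at -0.070.

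**Severity mediator not cut short by death** (such as early blood pressure). This was simulated with 2,000,000 babies: DCC shifts the mediator by -0.25 SD; logit of transfusion = 0.4 + 1.0 × mediator - 0.1 × DCC; untransfused death rises with the mediator. All coefficients are assumed. ACME is the average causal mediation effect.

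| Untransfused deaths, ICC / DCC | ACME, no such deaths | ACME, deaths coded 0 | Proportion mediated |
|---|---|---|---|
| 1.0% / 0.7% | -0.051 | -0.048 | 71% to 70% |
| 3.0% / 2.2% | -0.051 | -0.044 | 72% to 70% |
| 5.0% / 3.7% | -0.051 | -0.039 | 72% to 66% |

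The ACME shrinks by about 5% to 24%; the proportion mediated moves much less. If death is unrelated to severity and equal between arms (3% each), the loss is about 3% and the proportion is unchanged.

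**Severity mediator cut short by death.** Sample volume is accumulated over the hospital stay, and sampling line is measured by total duration. A baby dying on day 1 has a low value on both together with an outcome of zero, which steepens the slope. In a separate simulation (1,000,000 babies, true RD about -0.072, untransfused deaths 4.3% with ICC and 3.5% with DCC, duration cut at day 1; all assumed), the log-duration slope rose from 1.28 to 1.40 and the proportion mediated from 58% to 62%. The ACME itself fell by 3 to 5%, less than the total effect.

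**Composite.** In the first simulation at 3.0% and 2.2%, coding deaths as 0 gave RD -0.063 and ACME -0.044. Counting transfusion or death gave -0.071 and -0.052, close to the values without such deaths (-0.071 and -0.051). This depends on death being tied to severity. When death was unrelated to it, the composite gained nothing (RD -0.069 either way).

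**The case against.** The article never says that babies who die untransfused are coded as zero. That is an inference from the outcome definition and the population. A fuller analysis plan may set a rule, and silence in a condensed article is not in itself a fault. Mediators must also be measured before the outcome, so some very early deaths may lack a usable value and drop out of those models. In the first simulation at 3.0% and 2.2%, excluding such babies gave RD -0.069 and ACME -0.050, a much smaller distortion. All this stands. The point survives because the article fixes the outcome and population and lists its sensitivity analyses in detail, and death is absent from each although the article itself says treatment changes it.

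As a contrast of transfusions actually received, the randomized total effect is valid. That also stands: the distortion exists only relative to need.

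A reader might infer that the severity pathway must be understated relative to placental transfusion. The documents do not support this. For cumulative sample volume and line duration the slope and proportion mediated can rise, and no calculation here models hematocrit, which deaths among babies with low values could also attenuate. Nor does the document supply any death rate from which to claim a definite percentage loss.

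Finally, a composite brings DCC's effect on survival into the indirect effect and so answers a different question. That is a reason to report it beside the primary outcome, not in its place.

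**Conclusion.** The concern holds in a limited form. The outcomes are defined per baby in all randomized babies with data, with no handling of death, in a study that aims to explain need for transfusion and reports a treatment effect on death. Relative to need, the total effect can be distorted, toward the null if untransfused deaths are commoner with ICC. Mediation by early severity markers may be attenuated, while slopes and proportions mediated for cumulative markers may be inflated.

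The size is unknown from the documents. Under the assumptions above it is small if about 1% die untransfused and material at about 3 to 5%. It rests on the literal coding, on the assumed untransfused deaths in each arm, and on how closely such deaths follow severity.

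**What to change.** Keep the primary outcome as it is. Then:

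- State how a baby who dies before any transfusion is counted for the any, number and volume outcomes.
- Tabulate deaths before first transfusion by arm. This alone shows whether the issue is negligible.
- Add to the listed sensitivity analyses the same total-effect and mediation models for red cell transfusion or death before transfusion. Report them beside the primary results, and qualify the mechanistic conclusion if they differ.

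The cost is one extra set of models, using death dates from the trial or hospital records. The drawback is that the composite mixes two events, so it should not replace the primary outcome.

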## Materials and methods

Study design

The study is a nested retrospective study, called the Transfusions in the APTS Newborns Study (TITANS) (study registration: ACTRN12620000195954), of the cohort of babies who were enrolled and randomly assigned to ICC or DCC in the Australian and New Zealand (NZ) sites for APTS (study registration: ACTRN12610000633088). This design has been developed to take advantage of the comprehensive dataset already collected for APTS, and because there is currently no suitable prospective study that could address the same research questions in such a large group of participants.

Babies had been considered eligible for APTS if obstetricians or maternal-fetal medicine specialists anticipated that delivery would occur before 30 weeks of gestation. Exclusion criteria included fetal hemolytic disease, hydrops fetalis, twin-twin transfusion, genetic syndromes, and potentially lethal malformations. Further details are available in the original APTS publication [15]. In the present TITANS analysis, we will also exclude any baby with a diagnosis of hemolytic anemia or aplastic/hypoplastic anemia.

Recruitment and data collection

There were 1401 babies enrolled for APTS from the 13 Australian and 5 NZ hospital sites [15]. APTS data was provided to the TITANS team on 31 July, 2020. It is planned to collect additional data from Australian and NZ APTS sites using a customised, secure web-based database application (REDCap) [20], which is maintained by the University of Sydney, Sydney, Australia. Data will be obtained from source documents (patient hospital records and laboratory reports) using the electronic data collection application from each study site. The individual participant data collected will correspond to the minimum data required to answer the research questions. Baby identification (ID) and other babies’ details from APTS will be used to re-identify participants and link them to hospital records. Identified data will be collected, in order to allow linkage between the data newly collected from patient records and hospital laboratories and the existing APTS dataset. The data will be checked with respect to range, internal consistency, consistency with published reports and missing items. After data cleaning and analysis, data will be stored in re-identifiable form, with each participant’s data being identified with the same study numbering system as used for the APTS study.

Objectives

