We will apply single mediator models on both placental transfusion variables and initial severity of illness variables if mediators are statistically independent, as seen in Table 1. Independence will be tested using linear regression and any appropriate link functions. If both mediators are not statistically independent, we will investigate the possibility of multiple mediator models, which require an expanded framework for analysis [21]. Here we assume that initial severity of illness is causally related to placental transfusion. For this process, we will use the method developed by Imai and Yamamoto [21] to estimate the ACME and ADE. Following this, 95%CI will be estimated with 1000 bootstrap simulations. If theoretical and empirical timing data and sensitivity analyses suggest that M1 and M2 have non-causal correlation and may be affected by an unmeasured latent mediator, we will adjust our approach to estimate interventional direct and path-specific indirect effects [27,28].

**Table 1 TAB1:** Overview of all mediation models * These variables will only be explored if a sufficient number of babies had both M1 and M2 measured ICC: immediate cord clamping; DCC: delayed cord clamping; Hct: hematocrit; vol: volume; n: number; mech: mechanical; vent: ventilation; O2: oxygen

Model	X - Intervention cord clamping	M_1_ - Mediator 1 placental transfusion	M_2_ - Mediator 2 initial severity of illness	Y - Outcome blood transfusions
If M_1 _is statistically independent of M_2 _after adjusting for covariates:				
1.0	ICC / DCC	Peak Hct	-	Transfusions any/vol/n
1.1	ICC / DCC	Admission Hct	-	Transfusions any/vol/n
1.2	ICC / DCC	Day 1 Hct	-	Transfusions any/vol/n
2.0	ICC / DCC	-	Mech vent or Inspired O2	Transfusions any/vol/n
2.1	ICC / DCC	-	Sampling line total duration	Transfusions any/vol/n
2.2	ICC / DCC	-	Sampling line yes/no	Transfusions any/vol/n
2.3	ICC / DCC	-	Cumulative blood sample volume	Transfusions any/vol/n
2.4	ICC / DCC	-	Blood pressure	Transfusions any/vol/n
If M_1 _is not statistically independent of M_2 _after adjusting for covariates:				
3.0	ICC / DCC	Hct peak	Mech vent or Inspired O2	Transfusions any/vol/n
3.1	ICC / DCC	Hct peak	Sampling line total duration	Transfusions any/vol/n
3.2	ICC / DCC	Hct peak	Blood pressure	Transfusions any/vol/n
3.3	ICC / DCC	remaining Hct variables*	Mech vent or Inspired O2	Transfusions any/vol/n
3.4	ICC / DCC	remaining Hct variables*	Sampling line total duration	Transfusions any/vol/n

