3.5	ICC / DCC	remaining Hct variables*	Blood pressure	Transfusions any/vol/n

Sensitivity analyses have been limited to a set of biologically plausible and clinically meaningful groups that will be explored by including them for adjustment with covariates, and with the introduction of interaction terms if appropriate. Missing data will be described, reasons for missing data will be explored, and the impact of missing data on conclusions about the treatment effect on the primary outcome will also be explored where possible (e.g., using sensitivity analyses and multiple imputation techniques).

Methodological Assumptions

The causal mediation approach assumes sequential ignorability: that the treatment effect on the outcome is not confounding and that the mediator effect on the outcome is not confounded. As treatment was randomly allocated to neonates, we will assume that the treatment-mediator relationship is not confounded. However, the mediator itself has not been randomized. Thus, unknown confounders may be driving a spurious effect in the mediator-outcome relationship. We will employ additional sensitivity analyses to estimate whether any mediation effects are sensitive to the violation of the assumption of sequential ignorability. To test the possibility of unmeasured confounders we will examine the correlation between residuals in the mediator model and the outcome model. If there is no correlation this would suggest there is no unmeasured confounding, if there is correlation between the residuals, an unmeasured mediator may be affecting both the measured mediator and the outcome. We will apply the method developed by Imai et al. and Tingley et al. [23,26] that uses sensitivity analyses to evaluate if the ACME estimate is sensitive to unmeasured confounding.

Post-randomization confounders are dependent on the treatment allocated, affect both mediator and outcome, and can corrupt the mediation estimate. In the context of the present trial, it is possible that non-adherence to the intervention is a post-randomization confounder. We are analyzing our data based on intention to treat principles; however, a sensitivity analysis based on the actual time of cord clamping to assess the influence of non-adherence with the treatment protocol on our estimates may be performed.

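### The covariate list leaves sex, delivery mode and hospital out of the main mediation models, and hospital is built into the mediator of Model 2.3

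*Protocol article*

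**What the plan says.** All references are to the protocol article.

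- **Covariates.** The Potential Confounders (Covariates) paragraph reads: "The following covariates may be used for adjustment in the analysis: gestational age at randomization before birth and any oral iron supplement pre-transfusion". The list is optional. The Objectives nevertheless promise results adjusted for prior risk factors and point forward to a list.
- **Sex and delivery mode.** These come under the heading "Sensitivity Analyses (For the Primary Outcome Analysis Only", where the text reads "Sensitivity analyses will adjust for the following variables: gender, birth <27 weeks vs. ≥27 weeks, method of delivery (vaginal versus cesarean". The same sentence goes on to intraventricular hemorrhage (IVH), surgery for patent ductus arteriosus (PDA), necrotizing enterocolitis (NEC) and sodium in the first 24 hours, all of which arise after randomization.
- **Hospital.** It appears in no covariate, sensitivity, model or clustering statement. The generalized estimating equations in the Data Analysis Plan deal with multiple births only. The babies come from "13 Australian and 5 NZ hospital sites".
- **The sample-volume mediator.** Putative Mediators defines it as "number of blood tests multiplied by hospital’s usual sample volume for each type of test". Table 1 uses "Cumulative blood sample volume" as the mediator of Model 2.3 and of no other model.
- **The known weak point.** Methodological Assumptions concedes that "the mediator itself has not been randomized" and plans a residual-correlation sensitivity analysis of the ACME.

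**The concern.** Randomization protects the comparison of arms on the mediator and on transfusion. It does not protect the association between mediator and transfusion within an arm, and the ACME and ADE both use that association. It has to be defended by adjusting for causes of both variables that precede the mediator. Sex and delivery mode are candidates that are already planned variables. As listed, they never enter the models for number or volume of transfusions. For the primary outcome they enter only in analyses that also adjust for later events, so no clean baseline-adjusted estimate is promised.

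Hospital is a further candidate. In Model 2.3 part of the variation in the mediator is the hospital's usual draw per test, yet the article labels the variable as initial severity of illness. If hospitals that draw more (or less) per test also transfuse more (or less) readily for other reasons, part of the estimated mediation compares hospitals rather than babies. Objectives 2 and 4, on mediation through severity and on the direct effect, would both be affected.

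There is also a knock-on effect. Table 1 chooses between single- and multiple-mediator models by whether M1 and M2 are independent after covariate adjustment. An optional covariate set leaves that choice open as well.

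**Working it through.** The article states no figure on this point, so there is none to reproduce. The check asks how omitting hospital acts on Model 2.3.

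**From the article:** 1401 babies; 13 + 5 = 18 hospitals; mediator = number of tests × hospital volume, so on the log scale log M = log(tests) + hospital multiplier.

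**Assumed, not in the article:** SD of log tests within arm σ = 0.5; effect of deferred clamping on log tests a = −0.15; mediator-outcome slope β = 0.20 on the risk scale; direct effect −0.03; SD of the hospital log multiplier s = 0.2 to 0.4; SD of hospital transfusion risk h = 0.05 or 0.10; correlation between the two ρ = −0.5, 0 or +0.5. True ACME = a × β = −0.15 × 0.20 = −0.030.

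With linear models, the slope estimated without hospital is:

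- if only the number of tests affects transfusion: (βσ² + ρsh) / (σ² + s²)
- if the volume drawn itself affects transfusion: β + ρsh / (σ² + s²)

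**Reading 1, number of tests only.** At ρ = 0 and s = 0.2, the slope is 0.05/0.29 = 0.172 and the ACME −0.15 × 0.172 = −0.026. At ρ = 0 and s = 0.4, it is 0.05/0.41 = 0.122 and −0.018. At ρ = −0.5, s = 0.35, h = 0.10, it is (0.05 − 0.0175)/0.3725 = 0.087 and −0.013.

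**Reading 2, volume itself.** At ρ = 0 the slope is 0.20 and there is no bias. At ρ = ±0.5, h = 0.10, s = 0.2, the shift is ±0.01/0.29 = ±0.034, so the ACME is −0.025 or −0.035. At s = 0.35 the shift is ±0.0175/0.3725 = ±0.047, so the ACME is −0.023 or −0.037, about 23% either way.

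Simulations with 1401 babies in 18 hospitals agree:

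| Reading | ACME without hospital (true −0.030) |
|---|---|
| Tests only, s = 0.2 or 0.4 | −0.012 to −0.031 |
| Tests only, s = 0.2 or 0.35, h = 0.10 | −0.014 to −0.031 |
| Volume itself, ρ = 0 | −0.030 |
| Volume itself, ρ = −0.5 | −0.023 to −0.025 |
| Volume itself, ρ = +0.5 | −0.035 to −0.037 |

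Under reading 1, coverage of the 95% interval for the slope was 3% to 94% without hospital. With hospital terms in both models it was 96% to 97%, and the ACME returned to −0.030.

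In a linear model the total effect is fixed by randomization, here −0.030 + (−0.03) = −0.060, so whatever leaves the ACME goes to the ADE. An ACME of −0.012 would be reported with an ADE of about −0.048 instead of −0.030.

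**The case against.** Several objections carry weight.

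- **Condensed article.** Site terms are often left to an analysis plan that is not shown here. That would answer a complaint about missing detail. This article, however, has its own data analysis plan with an explicit confounder list and an explicit sensitivity list, and the point is that those lists are badly fixed. The wording is permissive, so it cannot be said that the authors will adjust for these two variables and nothing else.
- **Sex and delivery mode are partly covered.** For the primary outcome the sensitivity analyses are a firm commitment. The gap is complete only for the secondary outcomes. No size can be given for either variable.
- **Reach of the multiplier.** It enters Model 2.3 only, and that model runs only if M1 and M2 are judged independent. The hematocrit models and Models 3.0 to 3.5 contain no such term. A reader might infer that every main ACME and ADE is confounded by hospital; the document does not support that.
- **Common cause not shown.** A reader might also take hospital to be an established common cause. A multiplier inside a mediator is not confounding by itself, and the article documents no differences between sites in sampling, line use, ventilation or transfusion.
- **Direction.** It is tempting to say that omitting hospital dilutes the mediated effect by half. That holds only if volume drawn has no effect of its own. Blood removed is a physical exposure, and if it drives transfusion the bias may be zero or go either way.
- **Existing safeguard.** The planned residual-correlation analysis addresses unmeasured confounding. It is useful, but it does not replace adjusting for variables already held.

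**Conclusion.** The point stands as a recommended improvement, not as a demonstrated bias. Followed as written, the lists leave pre-mediator variables that the study holds out of the main mediator and outcome models. In Model 2.3, one of them is part of the mediator by construction.

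Size and direction cannot be derived from the document. Under the assumed hospital variation, the Model 2.3 bias lies between none and roughly a quarter in either direction if sampled volume itself drives transfusion. If only the number of tests matters, it ranges from almost none to attenuation of about half: (0.030 − 0.014)/0.030 = 53% at a multiplier SD of up to 0.35, and (0.030 − 0.012)/0.030 = 60% in the most extreme scenario run, at SD 0.4. For the other mediators, the concern depends on site differences in practice that are plausible but undocumented.

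Nothing here settles whether oral iron belongs in the list or whether a separate term for multiple birth is needed. Those are different questions.

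**What to change.** - State that gestational age, sex, mode of delivery and hospital *will* be included in both the mediator and the outcome model, for all transfusion outcomes. Hospital can be indicator terms with the smallest sites pooled, or a hospital effect.
- Use the same fixed set when testing whether M1 and M2 are independent.
- Move IVH, PDA surgery, NEC and 24-hour sodium into separate sensitivity analyses, so that baseline adjustment is never mixed with adjustment for later events.
- For Model 2.3, say whether the mediator is meant as severity (number of tests) or as blood removed (volume), since the effect of omitting hospital depends on it.

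No new data should be needed: sex and delivery mode are already planned variables, and records are collected by site. The cost is 18 − 1 = 17 hospital terms at most, for up to 1401 babies (about 1401/18 = 78 per hospital on average), with a small loss of precision.
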